**Table 3 Tab3:** **Households allocated to each net product per village and district in the prospective study**

	Olyset ^®^	PermaNet ^®^2.0	Netprotect ^®^	Total
Districts	8	8	8	8
Villages per district*	10	10	10	10
Households per village	15	15	15	45
Total households	1,140	1,140	1,140	3,420
Total nets**	3,420	3,420	3,420	10,260

*Ten villages selected per district, except for Kinondoni (Dar es Salaam) district with only 6 villages.

**Assuming an average number of 3 nets per households based on the average number of sleeping spaces in households in Tanzania.

A questionnaire will be conducted in Kiswahili, the local language spoken throughout Tanzania, with household heads, or another adult, by the field team (Additional file 2). Respondents will be asked whether they received nets during two NMCP campaigns in 2009-2011. Nets from the campaigns are identifiable by their light-blue colour and size (single), allowing us to differentiate those nets from the campaign and those that might have come from the private sector or Non-Governmental Organisations (NGOs). We will individually assess every net returned to the storage facilities at Bagamoyo Research and Training Centre (BRTC) for its brand label, colour, size, level of cleanliness, and age of manufacture, if available. From those retrospective nets, 200 Olyset^®^ campaign nets will be randomly selected using the ‘sample’ function in R 3.1.1 for durability testing in the laboratory and semi-field systems (Figure 1; Table 1). All other collected Olyset^®^ nets will be recycled by A to Z Textile Mills Ltd (http://www.azpfl.com/index.php/en/).

#### Prospective study

Attrition, net use and user behaviour (Additional file 2), and physical degradation of study nets will be assessed in every consenting household at three subsequent sampling points (10, 22, and 36 months) after the initial LLIN distribution. All households will be surveyed for attrition and a sub-sample of three nets per household will be assessed for physical degradation. Field interviewers will be trained using an amended version of a recently developed USAID/NetWorks-supported training tool kit to assess the number of different category sized holes under field conditions [33].

At each time point, all nets from 48 randomly selected households for each net product will be taken for sub-sampling to validate the D component (physical degradation) assessment in the laboratory, and for B (biological efficacy against mosquitoes) and C (HPLC analysis) components efficacy testing (Figure 1). These households will be randomly selected stratified by district and LLIN product so that six nets from each district per product are evaluated for BCD components. All sampled nets will be replaced with new nets of the same kind except for Netprotect^®^ nets which will be replaced by Olyset^®^, and the sampled household will be excluded from subsequent sampling rounds.

### ABCDR components

#### Attrition (A component)

Attrition of LLINs is defined as the proportion of LLINs that are no longer in use as mosquito nets to sleep under in the receiving household after a given amount of time. This is commonly due to loss through nets being damaged, discarded, or used for other purposes than sleeping under. Nets that are sold, given away or stolen will be excluded from the attrition analysis following WHO guidelines [6] as they may still be “serviceable”.

Trained field interviewers will perform the field visits of all households selected from the master list and voluntarily participating in the study during the sampling points (retrospective sampling, 10, 22 and 36 months after prospective LLIN distribution). Questionnaire data will be collected using Open Data Kit (ODK) Collect software (http://opendatakit.org/use/collect/) on Android tablet computers (Google Nexus One). Observations by the field workers on presence and absence of distributed nets, the location of the net (hanging or stored away), fabric integrity and the net condition are included in the questionnaire (Additional file 2).

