**Table 1 Tab1:** **LLIN durability components**

Component	Definition	Response variables for analysis
**A**ttrition	Net loss from household through discarding or use for alternative purpose	- Net presence.
**B**iological efficacy	Ability of net to incapacitate or kill anopheline mosquitoes after contact with insecticide	- Mosquito knockdown (%) 60 minutes post-exposure.
		- Mosquito mortality (%) 24 hours post-exposure.
		- Percentage of bloodfed mosquitoes.
**C**hemical residue	Amount of active ingredient in fibres	- Proportion of nets with active ingredient equal to WHO standard g/kg
**P**hysical degradation	Physical state of the net defined through number, size and location of holes to estimate protection against mosquito bites	- Proportionate Hole Index (pHI) / hole area by location on net.
		- Proportion of nets with a pHI exceeding ≥643 [6].

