**net products distributed in the study**

Product name	Product type	Insecticide concentration	Denier	Manufacturer	WHO approval	Reference
Olyset^®^	Permethrin **incorporated** into polyethylene	780 mg/m^2^	>150 denier	Sumitomo Chemicals	Full	[16]
PermaNet^®^ 2.0	Deltamethrin **coated** on polyester	55 mg/m^2^	100 denier	Vestergaard Frandsen	Full	[15]
Netprotect^®^	Deltamethrin **incorporated** into polyethylene	68 mg/m^2^	110 denier	BestNet	Withdrawn	[30, 31]

As a consequence of using LLIN products from different materials (Table 2), the nets may be able to be distinguished physically. However, each net type will be rectangular, of the same dimensions (190 cm x 180 cm x 150 cm) and colour (white) with six loops per net to prevent household participants, technical staff and field team from knowing the treatment allocation as much as possible. A waterproof unique identifying barcode and a five-digit serial number will be attached to each distributed LLIN with a self-laminating laser tag to a hanging loop of the net. This will allow tracking of the nets once they are distributed. The field team will record the net serial number on the questionnaire as the net is distributed to allow the matching up of household and unique net identifying numbers on the net master list.

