#### Retrospective study

Households will be enrolled on written informed consent (Additional file 1). Participants’ houses and questionnaires will be identified by barcodes associated with numeric codes (six-digit serial numbers) to ensure their anonymity and due care will be taken to ensure that only barcodes and numeric codes are used on LLINs and questionnaires, thus blinding participants and researchers to treatment allocation. All the nets from the participating households will be collected and replaced with one of the three new LLIN products (Table 2) chosen at random. The prospective LLIN products will only be known to field teams as net types 1, 2 and 3, thereby blinding and randomising the treatment distribution as much as possible. Each day the field team will receive a household list and a randomly mixed bundle of five sets of type 1, 2 and 3 nets (three nets of same type per set bagged for one household, assuming an average of three sleeping spaces per household). The interviewer will randomly pick one set from the bundle to be distributed when they arrive at each household (modified lottery method). If the household contains more than three sleeping spaces, more nets of the same type will be provided. The interviewer will record the five-digit serial numbers attached to the nets on the questionnaire as described above. Thus, randomisation is conducted by the field workers at the household level, resulting in 15 households per village receiving sufficient nets of one product to cover each sleeping space (Table 3).

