### Statistics and data analysis

#### Sample size calculation

Sample size calculations were based on the primary outcome measure of net attrition using the standard formula for the difference between two proportions [47]. The BCD components were treated as an additional sub-sample to the original calculated sample size. Assuming an average of 3 nets per household and a coefficient of variation of 0.25, then the formula on page 110 of Hayes & Moulton [48] gives a sample size of 973 households per arm to detect a difference in attrition between two brands with attrition rates of 47.5% and 52.5% with 90% power. Therefore, there will be at least 90% power to detect a 5% difference in attrition rates. Loss to follow up and households excluded due to sub-sampling have been added to the final sample size to give (1,140 households * 3 nets/ household) = 3,420 LLINs per LLIN product (Table 3).

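### Dropping nets reported as sold, given away or stolen from the primary attrition analysis is a post-randomisation exclusion that can bias the brand comparison, by an amount the protocol does not let one determine

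*Protocol article*

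**What the plan says.** The Sample size calculation section names net attrition as the primary outcome. The Data analysis section compares the three products by logistic regression at each prospective visit (10, 22 and 36 months). Allocation is by household: "randomisation is conducted by the field workers at the household level".

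The attrition section defines the outcome as the "proportion of LLINs that are no longer in use as mosquito nets to sleep under in the receiving household". It then adds: "Nets that are sold, given away or stolen will be excluded from the attrition analysis following WHO guidelines", because such nets may still be usable. Table 1 words the component as "Net loss from household through discarding or use for alternative purpose" and gives net presence as the response variable.

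On data sources, the attrition section lists "Observations by the field workers on presence and absence of distributed nets", together with net location and condition. The questionnaire is held "with household heads, or another adult, by the field team" (Retrospective study section, after Table 3), and the same additional file is cited for the prospective rounds. On blinding, the LLIN products section concedes that "the nets may be able to be distinguished physically".

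The sample size rests on this premise: "Assuming an average of 3 nets per household and a coefficient of variation of 0.25". The allowance added to reach 1,140 households per product names loss to follow-up and sub-sampling only.

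**The concern.** The rule takes nets out of both numerator and denominator according to what happened to them after allocation. Randomisation protects a comparison of all nets as allocated. It does not protect a comparison of the nets left after a selection that the product itself may influence. The products differ in material and can be told apart, so households may value them differently and pass them on at different rates or in different states of wear.

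An absent net cannot be inspected. That the reason for its absence comes from the household is an inference, but hardly any other source is available.

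The wording adds to the difficulty. A sold or stolen net is no longer in use in the receiving household, so it meets the text definition of attrition and is then excluded in the same paragraph. It is also absent under the net-presence response in Table 1. These readings give different numerators and denominators for the outcome that is meant to guide net procurement.

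**Working it through.** **1. The plan's own sample size.** Inputs from the Sample size calculation section: p0 = 0.475, p1 = 0.525, m = 3 nets per household, k = 0.25, 90% power. Alpha is not stated; two-sided 0.05 is assumed. The unmatched cluster formula for two proportions is

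c = 1 + (z_α/2 + z_β)² × [p0(1−p0)/m + p1(1−p1)/m + k²(p0² + p1²)] / (p0 − p1)²

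= 1 + 10.507 × (0.49875/3 + 0.03133)/0.0025 = 831.4, so 832 households per arm.

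The protocol states 973, which these inputs do not reproduce. The stated figure is the larger one, and 973 households give 93.9% power by this formula. That discrepancy is a separate matter.

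**2. Do exclusions undermine the power?** If 15% of nets were excluded (assumed), m = 3 × 0.85 = 2.55 and c = 1 + 10.507 × (0.49875/2.55 + 0.03133)/0.0025 = 954.7, so 955. This is below the stated 973 and below the 1,140 allocated.

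**3. Gap created when only serviceable nets are passed on.** Assume 50% of distributed nets are worn out or discarded in both brands, and a share e is excluded. Observed attrition is 0.5/(1 − e).

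| Excluded, brand A vs B | Observed A | Observed B | Gap (points) |
|---|---|---|---|
| 5% vs 8% | 52.6% | 54.3% | 1.7 |
| 5% vs 10% | 52.6% | 55.6% | 2.9 |

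**4. Gap created when only the reported reason differs.** Assume total loss is 50% in both brands. Observed attrition is (0.5 − e)/(1 − e). For 5% vs 8% this is 47.4% vs 45.7% (−1.7 points); for 5% vs 10% it is 47.4% vs 44.4% (−2.9 points). The size is the same and the sign is reversed, so the direction cannot be predicted.

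**5. Excess exclusion needed for 5 points.** Under step 3, e1 = 1 − 0.5/[0.5/(1 − e0) + 0.05].

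| e0 | e1 | Excess (points) |
|---|---|---|
| 0% | 9.1% | 9.1 |
| 5% | 13.2% | 8.2 |
| 10% | 17.4% | 7.4 |
| 20% | 25.9% | 5.9 |

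**6. Chance of a significant result.** With 973 households per arm, m = 3, k = 0.25 and two-sided 0.05, the 1.7-point artefact would be declared significant about 22–23% of the time and the 2.9-point artefact about 53–55%.

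**7. Equal discarding, independent passing-on.** Assume constant hazards over follow-up: discarding λ = ln 2 = 0.693 in both brands (50% discarded if nothing is passed on), and passing-on μ = 0.15 vs 0.30. The share passed on is μ/(λ+μ) × (1 − e^−(λ+μ)); the share discarded has λ in place of the leading μ.

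| | μ = 0.15 | μ = 0.30 | Gap (points) |
|---|---|---|---|
| Passed on | 10.1% | 19.0% | |
| Discarded, of all nets | 46.8% | 43.9% | −2.9 |
| Protocol rule: discarded/(1 − passed on) | 52.1% | 54.3% | about 2 |
| All-cause loss | 57.0% | 63.0% | +6.0 |

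A net already discarded cannot later be given away, so the nets passed on come from those that have survived so far. Unequal passing-on alone therefore moves the result.

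**8. The null case.** If the excluded nets contain the same proportion of worn-out nets as those kept, observed attrition stays at 50% in both brands and the gap is zero, whatever the exclusion rates.

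**The case against.** The rule is a pre-specified outcome definition, applied alike to all three products, with a stated reason and attributed to WHO guidance. It agrees with the Table 1 wording on discarding or alternative use. In a durability study, a usable net that is stolen or given to a relative is no evidence that the product wore out. Comparability with other durability studies is an explicit aim in the Discussion. All of this stands, and it is the reason to keep the measure.

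The alternatives are not neutral either. Suppose 40% of distributed nets are discarded in both brands and 10% vs 20% are passed on. The rule gives 40/90 = 44.4% vs 40/80 = 50.0%, a gap of 5.6 points. All-cause loss gives 50% vs 60%, a wider gap driven wholly by passing on. Discarding over all distributed nets gives 40% vs 40%, which would hide a real difference in wear if passing on were unrelated to condition. So no single replacement should displace the rule.

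A reader might infer from the 5.6 points that the exclusion produces an artefact as large as the target effect. The documents do not support that: they give no passing-on rates, and the example assumes that one brand is passed on twice as often. A reader might also infer that the stated power fails because fewer than three nets per household are analysed. It is not shown to fail (step 2), and three is an average, since larger households receive more nets.

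The suggestion that households find it easier to report a gift or theft than discarding or misuse is plausible, but nothing in the protocol supports it. Sensitivity analyses may be in a statistical analysis plan that is not available, so their absence from the article is not held against it. The reply that unrelated exclusion does no harm holds only in the sense of step 8. Step 7 shows that independence of the two hazards is not enough.

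**Conclusion.** The concern holds in a limited form. The protocol fixes a post-randomisation exclusion for its primary outcome that in practice rests on household report. It can bias the brand comparison, in either direction, if the share passed on or its relation to net condition differs by brand.

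The size is unknown. Under the stated assumptions it runs from zero, through 1.7 points (5% vs 8%) and 2.9 points (5% vs 10%), to the 5-point target at about 6 to 9 points of excess exclusion. It is about 2 points with equal independent discarding hazards and 10% vs 19% passed on. These figures assume true attrition near 50%, as in the sample size calculation, and in steps 3 to 5 exclusion drawn entirely from one condition group. Even a gap below 5 points matters, because a trial of this size could often declare it significant.

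**What to change.** Keep the WHO-style figure for comparison with other studies. Pre-specify beside it brand comparisons that retain all distributed nets in households still under follow-up:

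- all-cause loss from the household, using the net-presence response already in Table 1;
- cumulative incidence of discarded or repurposed nets, with sold, given away or stolen as a competing category; or a discrete-time survival analysis that censors passed-on nets instead of deleting them.

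If censoring is used, state how much of the interval a passed-on net contributes. A net passed on before the 10-month visit that contributes nothing is treated exactly as under the present rule. Censoring also assumes that passing on is unrelated to condition.

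Report the passed-on share by brand and visit, and draw a brand conclusion on attrition only if it is consistent across these analyses. Align the text definition with Table 1, so that it is clear which nets enter numerator and denominator.

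No new data should be needed, because applying the exclusion already requires the reason for loss. The cost is a few more analysis lines, and figures that answer slightly different questions and must be read together.

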#### Physical degradation (D component)

The physical degradation, or integrity, of the nets will be measured by counting the number, location and size of hole(s) in each net. The proportional hole index (pHI) will be calculated using the hole size categories as per WHO guidelines [5, 6] (Table 4). In addition to the different category sized holes, we will also include five different hole locations on the net by dividing the side panels of the net into a total of four zones from top to bottom, each measuring 37.5 cm, and counting holes in the roof separately as a fifth location (Figure 3). Mosquitoes are more likely to aggregate around certain locations on occupied bed nets (e.g. the roof; [34]). In addition, the lower edges of the bed nets are more likely to be severely damaged, but they are also more likely to be tucked in at night, potentially avoiding mosquito entry [35]. By counting the holes by location, we will be able to take into account these factors when analysing the hole index data and give different weights to holes in different locations. To our knowledge, this formula has not yet been developed. One of our aims is therefore to incorporate hole location into the equation, and to compare its relative importance to a simpler model in terms of protection against mosquitoes in semi-field experiments. Holes will be counted both in the laboratory and in the field using a collapsible metal frame made out of locally available economical materials (Figure 3). In the field, holes in a maximum of three prospective nets will be counted per household due to logistical and time constraints.

**Table 4 Tab4:** **Hole size categories and their proportionate weights**

Hole category	Hole size description	Hole size (cm)	Hole diameter (cm)	Weight ^a^
**Size 1**	Smaller than a thumb (finger)	0.5-2	1.25	1
**Size 2**	Larger than a thumb but smaller than fist (hand)	2-10	6	23
**Size 3**	Larger than a fist but smaller than a head (head)	10-25	17.5	196
**Size 4**	Larger than a head	>25	30 (assumed)	578

^a^Area of hole divided by 1.23 [6].

**Figure 3 Fig3:**
[figure not shown]
**Mosquito net hole counting by zone.** Collapsible metal frame (170 cm x 180 cm x 190 cm) using locally available materials divided into four 37.5 cm zones from the top to the bottom in order to count holes by zone under laboratory and field conditions.

#### Biological efficacy (B Component)

Testing will be performed at BRTC, Bagamoyo, Tanzania using *An. gambiae* sensu stricto (s.s.) (Ifakara strain, Njage 1996) mosquitoes that are fully susceptible to insecticides and are reared according to CDC guidelines [36]. Mosquitoes used for testing will be 2-8 days old (depending on the test), nulliparous sugar fed females. Standard WHO cone bioassays will be carried out to evaluate new nets at baseline (ten samples per net product), 200 retrospective Olyset^®^ nets, and a random sub-sample of 48 prospective nets per time point. WHO tunnel tests will be performed if nets fail the cone test [7, 37]. To validate these WHO recommended bioassays and help to estimate fully the protection provided by nets under user conditions, those 48 nets will first be tested in a semi-field tunnel (SFT) – the newly developed Ifakara Tunnel Test (ITT) - to measure the protective efficacy of the nets to people resting underneath them [38]. For the WHO tunnel test and ITT, only those mosquitoes that are responsive to human odour on the day of testing will be used. For semi-field tests, mosquitoes will be deprived of sugar solution for six hours prior to experiments and transferred to a screened test cage one hour prior to testing to allow them to acclimatise.

##### Ifakara tunnel test (ITT)

A semi-field enclosure is here defined as an enclosed environment, ideally situated within the natural ecosystem of the target disease vector and exposed to ambient environmental conditions. Semi-field enclosures offer several useful features: 1) participants are safe because they are exposed only to laboratory-reared disease-free mosquitoes, 2) experiments can be run using standard numbers of mosquitoes allowing year round collections regardless of natural vector populations, and 3) using mosquitoes of known age, physiological status and avidity reduces experimental variability allowing for rapid data collection and improved data quality.

The Ifakara tunnel is a 50 m long, 3 m wide and 2.1 m high steel tube frame construction covered by durable UV resistant polyurethane coated netting (Figure 4A). The structure is constructed upon a concrete base surrounded by a water channel to prevent entry by ants and spiders. The tunnel sits beneath a simple beamed wooden frame supporting a corrugated steel roof to allow work in all weather conditions. The netted tunnel is divided into ten individual test chambers (5 m x 3 m x 2.1 m) with interconnecting doors that are sealed with zips and Velcro to prevent mosquitoes moving from one test chamber to another (Figure 4B). Each end of the tunnel contains an additional double door module to prevent loss of laboratory-reared mosquitoes into the wild. Mosquitoes will be released within each compartment by raising the netted holding cages from their removable wooden bases. This is achieved remotely by the volunteer in each compartment pulling a nylon cord to raise the cage whilst remaining beneath the net (Figure 4C). After the allotted experimental time period, all mosquitoes within each of the compartments will be removed by mechanical aspiration (Figure 4D).

